### **6.4.2 Product accountability and reconciliation**

All study formula received by the investigator must be inventoried and accounted for throughout the study period on the corresponding Study Formula Inventory Forms (Appendix 15.4) by the study team in Belgrade. The dispensed study formula to the subjects must be inventoried and accounted for throughout the study period on the corresponding Study Formula Accountability Form that is part of the CRF (Appendix 15.12).

These two forms will be monitored.

The study formula must not be given to any person except the study personnel and subjects participating in this study.

Unused formula must not be traded. Infant formula which has not been used by the parents / caregivers has to be given back to the investigators. At the end of the study, all used and unused study formula must be accounted for on the Study Formula Accountability Forms as well. Unused products left in the hospital can be returned via the HiPP representative in Serbia for destruction or the hospital can arrange for its destruction at the end of the study. Destruction must be documented in the study formula inventory from.

## 7 Definition of measures

### 7.1 Primary Outcome

The primary outcome of the study is the average daily weight gain in grams (g/d) between Visit 1 (30 ± 2 days of life) and Visit 4 (120 ± 3 days of life).

The weight in grams will be assessed at each Visit by responsible study person and average daily weight gain in g/d during the study period will be calculated.

### 7.2 Secondary Outcomes

#### 7.2.1 Anthropometric data

In the context of all paediatricians' examinations anthropometric data such as length (cm) and head circumference (cm) will be recorded.

#### 7.2.2 Protein status measurements

At Baseline Visit and the final Visit 4 blood will be drawn to assess protein status and metabolism with following parameters:

- serum albumin
- serum creatinine
- blood urea nitrogen
- plasma amino acid profile (Appendix 15.15)

#### 7.2.3 Fatty acid profile in plasma

At Baseline Visit and the final Visit 4 blood will be drawn and the profile of defined fatty acids will be analyzed (Appendix 15.16).

### 7.3 Other measures

#### 7.3.1 Physical Examination

Status of the child will be examined in a clinical examination at every Visit. It will be determined if findings are normal or remarkable. The following will be covered:

- General appearance
- Skin
- Fontanel
- Ear/Nose/Throat
- Lymphoid nodules
- Heart
- Pulmo

- Abdomen
- Extremities
- CNS
- Others
- Medications necessary

### 7.3.2 Formula intake

In the context of the Visits, the reminder calls and the diaries filled out at home, formula intake will be reported by assessing:

- Visits/Reminder calls: formula meals per day, breastfeeding meals per day, meals of others
- Diaries:
  - number of bottles per day
  - intake of formula in ml per meal (documentation of prepared formula in ml and leftover in the bottle in ml)
  - acceptance of formula (good / reluctant / bad)

In the breastfeeding reference group similar dairies will have to be filled in asking also for feeding history (number of breast meals per day).

### 7.3.3 Tolerance

In the context of the diaries filled out at home formula tolerance will be reported by assessing:

- Stool characteristics
  - stool frequency: >5/day (very often), >3/day (often), 1-2/day (regularly), <1/day (not often), less than every third day (seldom)
  - stool colour: yellow, yellow-green-brown (mustard), green, brown, grey, other
  - stool consistency: hard lumps, sausage with cracks, soft sausage, mushy (like porridge), watery
- Digestion history
  - Regurgitation / vomiting
    - Regurgitation is observed when formula which has been previously consumed is brought back up through the oesophagus into the mouth. It has to be accounted by the parent / caregiver into the diary
    - Vomiting is defined as the expulsion of the refluxed gastric content into the mouth (choke and gush). It has to be accounted by the parent / caregiver into the diary

- Colic
  - Colic is defined as an abdominal pain, manifested by severe crying, drawing the legs up to the abdomen and distended and/or tense abdominal wall.
  - Frequency during the past day is reported as: not at all, <3 hours/day, >3 day hours/day
- Flatulence
  - Flatulence is defined as excessive bowel air and related discomfort.
  - Frequency during the past day is reported as: not at all, < 3 hours, 3-6 hours, 6-12 hours, >12 hours / day

In the breastfeeding reference group similar dairies will have to be filled in asking also for stool characteristics and digestion history.

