**Secondary outcomes**

- Anthropometric data:  
length (cm), head circumference (cm)
- Protein status measurements:  
serum albumin, creatinine, blood urea nitrogen, plasma amino acid profile
- Fatty acid profile in plasma
- Formula intake, acceptance and tolerance
- Stool characteristics

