## **8.6 Diaries**

Three days before each Visit (except Baseline Visit) parents / caregivers are asked to fill out a diary at home. Diaries for the formulae groups and the reference breastfeeding group differ slightly (Appendix 15.13).

Parents / caregivers of the formulae groups are asked to write down bottle feeding, concomitant diet and tolerance as defined in chapter 7.3.1. Parents / caregivers of the breastfeeding group are asked to write down number of breast meals, concomitant diet and tolerance.

Diaries will be brought back to the paediatrician at the next study Visit. It will be checked for correct filling out and if necessary entries will be discussed.

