### 9.4 Secondary outcome variables

Length gain: same calculation as for primary outcome

Gain in head circumference: same calculation as for primary outcome

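### As written, the tolerance scales have no band for exactly 3 stools a day or exactly 3 hours of colic, and exactly 6 hours of flatulence fits two bands

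*Protocol*

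**What the plan says.** Section 7.3.3 sets out the tolerance items and says where they come from: "In the context of the diaries filled out at home formula tolerance will be reported by assessing" a list of stool and digestion items.

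- Stool frequency: "stool frequency: >5/day (very often), >3/day (often), 1-2/day (regularly), <1/day (not often), less than every third day (seldom").
- Colic: "Frequency during the past day is reported as: not at all, <3 hours/day, >3 day hours/day".
- Flatulence: five answers, namely none, under 3 hours, 3-6 hours, 6-12 hours and over 12 hours.

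Parents complete the diary around each visit after baseline (section 8.6: "Three days before each Visit (except Baseline Visit) parents / caregivers are asked to fill out a diary at home"). The breastfed group answers the same kind of items: "In the breastfeeding reference group similar dairies will have to be filled in asking also for stool characteristics and digestion history".

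The status of these items differs between places. The synopsis lists "Stool characteristics" among the secondary outcomes, together with intake, acceptance and tolerance. In the body the items fall under "7.3 Other measures", not under 7.2. Section 9.4 names only two secondary variables, length gain ("Length gain: same calculation as for primary outcome") and gain in head circumference.

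No section gives a rule for values that fit no band or two bands, and 7.3.3 does not list a raw stool count. The diary form itself (Appendix 15.13) is named but not reproduced.

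**The concern.** A categorical scale should give every possible answer exactly one place. Three stools a day is an ordinary whole-number answer, yet the listed bands pass from 1-2 straight to more than 3. If the printed diary uses these bands, a parent with 3 to report can only pick a wrong neighbour or leave the item open. Because the protocol does not ask for the count, the true value could not be recovered at analysis. That makes this a question of what is collected, which an analysis plan cannot repair later.

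At stake is the clarity of the stool-frequency and tolerance comparisons. Between the two formula groups the error should mostly blur a difference. In the comparison with breastfed infants, the share of unclassifiable entries could itself differ if stool frequency differs.

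**Working it through.** The plan states no figure for this item, so there is none to reproduce. The check is whether each value falls in exactly one band.

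**Stool frequency.** Each band in 7.3.3 is treated as an interval.

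| Stools per day | Bands satisfied |
|---|---|
| fewer than 1 in 3 days | <1; less than every third day |
| 1 in 3 days, up to just under 1 | <1 |
| 1 to 2 | 1-2 |
| above 2, up to and including 3 | none |
| above 3, up to 5 | >3 |
| above 5 | >5; >3 |

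Among whole daily counts there is one gap, at 3. If a parent reports an average, values between 2 and 3 (2.5, for example) are also without a band. There are two overlaps, one at each end, and both are nested: >5 lies inside >3, and less than every third day lies inside <1.

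**Colic.** The bands are none, <3 hours and >3 hours. Exactly 3 hours satisfies none of them.

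**Flatulence.** The bands are none, <3, 3-6, 6-12 and >12 hours. Three hours fits only 3-6. Six hours fits both 3-6 and 6-12. Twelve hours fits only 6-12, because >12 excludes it.

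**Scale of the stool gap (assumption).** The documents give no distribution of stool frequency. If the daily count were Poisson with mean m, then P(exactly 3) = e^(-m) × m³ / 3!.

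| Assumed mean m | P(exactly 3) |
|---|---|
| 1 | e^(-1) × 1/6 = 6% |
| 2 | e^(-2) × 8/6 = 18% |
| 3 | e^(-3) × 27/6 = 22% |
| 4 | e^(-4) × 64/6 = 20% |
| 5 | e^(-5) × 125/6 = 14% |

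These figures show only that the gap need not be rare. They are not estimates for this trial. They also show why a comparison with the breastfed group could be affected unevenly: a group with mean 1 would have 6% of days unclassifiable and a group with mean 3 would have 22%.

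**Check of the repaired stool scale.** With >5, 3-5, 1-2, <1 but at least every third day, and less than every third day, the counts 1 and 2 go to 1-2, the counts 3, 4 and 5 go to 3-5, and 6 or more goes to >5. Infrequent stools go to one of the last two bands. Each whole count has one place, and 5 a day stays in the band it has now.

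**The case against.** The best case against the point is that it is a wording slip in a minor item, on a form nobody can see here. Several parts of that case stand.

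- **The form is not shown.** Section 8.5.1.9 says instructions are printed on the diary, so the form may word the bands differently or settle the gap. That parents actually guessed or left blanks is therefore not established. The finding concerns the protocol text.
- **Diaries are reviewed.** Sections 8.5.2.6 and 8.6 have entries checked, discussed and completed where possible. This may reduce missing answers, but it cannot supply a band that does not exist.
- **The overlaps matter little.** With ordered labels running from very often to seldom, the natural reading is that the more extreme band applies. Only the gap at 3 is substantive.
- **Status.** Secondary standing rests on the synopsis alone, and the stated objectives contain no tolerance hypothesis.

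A reader might infer that the whole stool outcome is misclassified. The text does not support that: colour and consistency have their own scales, and the frequency gap is confined to 3 a day (or averages above 2 and up to 3). A reader might also think that the flatulence bands overlap at 12 hours; they do not.

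What survives is that, as written, the scale cannot hold an ordinary answer and no other section resolves it.

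**Conclusion.** The point holds in a narrow form and is minor. Section 7.3.3 leaves exactly 3 stools a day and exactly 3 hours of colic without a band and gives exactly 6 hours of flatulence two. The nested stool bands lack a stated rule but are readable.

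The share of entries affected is unknown; the 6% to 22% for stool frequency rests wholly on the assumed Poisson counts with means of 1 to 5. The expectation that error between the formula groups blurs rather than biases rests on their blinding (section 6.1.5). The comparison with the breastfed group has no such protection. Weight gain, the sample size and the non-inferiority conclusion are not touched, and it would be wrong to read this as undermining the trial's growth claim.

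**What to change.** 1. In 7.3.3, make the stool bands exhaustive and exclusive while keeping the top cut-off: >5, 3-5, 1-2, <1 a day but at least every third day, and less than every third day. Alternatively record the daily count and band it afterwards. The count is safer, because the bands above still need a rounding rule if parents give averages such as 2.5.
2. Assign exactly 3 hours of colic to one band and exactly 6 hours of flatulence to one band.
3. Check Appendix 15.13 for the same wording and correct it if present.
4. State once whether these items are secondary outcomes or other measures, so that the synopsis, section 7 and section 9.4 agree.
5. For completed diaries, write a coding rule for blank, double-marked or annotated entries, fixed without reference to formula group, with the more extreme band applying where bands are nested. It cannot identify a 3 that a parent silently placed in a neighbouring band, so that limit should be reported.

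Before use, the cost is a reprinted diary page. Amendment No. 3 reports the intervention period as finished, so for these data the practical cost is the coding rule and a sentence on the limitation.

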#### 7.3.4 Compliance to study protocol

Compliance to the study protocol will be checked during each clinical study Visit and during the telephone interview. It must be made sure, that:

- No other Formula but the study formulae is given to the formula group infants
- **Full breastfeeding** or **full formula-feeding** (Definition see Chapter 5.4.1), respectively, is maintained
- The above mentioned aspect will be clarified by asking for breast milk meals per day, formula meals per day and any concomitant meals in the CRF
- Absence of any unauthorized concomitant diet (excessive additional liquid intake, complementary food)

#### 7.3.5 Health observations

The paediatrician is requested to report health associated observations during the last 4 weeks (time period between the visits, reported by parents/caregivers) at each clinical study Visit. Health observations and -if used- medication must be documented in the CRF. Health observations are for example:

- nappy rash
- skin problems
- slimy stools
- infections

#### 7.3.6 Formula associated observations

Formula associated observations will be recorded during each clinical study Visit and during the telephone interview:

- Formula acceptance of the subject should be reported as good / reluctant / bad.

If “reluctant” or “bad” is marked with a cross, the investigator should ask for the reason why and record the reason in the respective space in the CRF/Telephone interview protocol.

- Formula handling should be reported as good / moderate / bad

If “moderate” or “bad” is marked with a cross, the investigator should ask for the reason why and record the reason in the respective space in the CRF/Telephone interview protocol.

## 8 Conduct of the study

### 8.1 Study plan, flow chart

See Flow Chart (Appendix 15.4) and Time Event Schedule in the appendix (Appendix 15.6).

### 8.2 Time schedule

The expected duration of the study will be approximately 26 month. Four months will be needed for preparation of the documents, study organisation and study initiation at study site. At the beginning of June 2009 the first subject will be enrolled in the study. Recruitment of the subjects is estimated to take 12 months (1 year). The latest subject will finish the study 16 month after start of recruitment. After termination of the study, another 6 month will be needed for laboratory analyses, evaluation of the findings and writing the final study report.

#### Time schedule of duration

| month    | 1                    | 2                                         | 3 | 4 | 5 - 20                                 |  |  |  |  |  | 21                           | 22 | 23 | 24                         | 25 | 26 |
|----------|----------------------|-------------------------------------------|---|---|----------------------------------------|--|--|--|--|--|------------------------------|----|----|----------------------------|----|----|
| activity | Document preparation |                                           |   |   |                                        |  |  |  |  |  |                              |    |    |                            |    |    |
|          |                      | Study organisation and initiation at Site |   |   |                                        |  |  |  |  |  |                              |    |    |                            |    |    |
|          |                      |                                           |   |   | Recruitment of subjects + intervention |  |  |  |  |  |                              |    |    |                            |    |    |
|          |                      |                                           |   |   |                                        |  |  |  |  |  | Labor. analyses + Evaluation |    |    |                            |    |    |
|          |                      |                                           |   |   |                                        |  |  |  |  |  |                              |    |    | Final report / Publication |    |    |

### 8.3 Study initiation Visit

Prior to study start, the entire study team will be educated by the Monitor regarding the study design and study requirements during a study initiation Visit. The Principal Investigator is responsible to train new study staff members according the study protocol. All people that are delegated by the Principal Investigator to conduct specific duties during the BeMIM study must sign the Signature Sheet. The name of the delegated person as well as the conducted duties must be written in this sheet.

### 8.4 Parent information, Subject recruitment and Randomisation

Parents / caregivers will receive information about the study before birth or within the first few days after birth (from birth to the 5th day of life) at the study site from a member of the study team. In case of interest, parents / caregivers will get contact information and are asked to get in touch with the study team. In compliance with the CONSORT statement the number of subjects assessed for eligibility will be reported (Subject Screening list).

Shortly before Baseline Visit parents / caregivers will receive Parent Information and an Informed Consent form from the study team (Appendix 15.7; Appendix 15.8).

The informing conversation should be made by educated study staff, the paediatric physician primarily involved in conducting the study or by a colleague paediatric or obstetric physician that is familiar with the study design and is able to answer parents / caregivers questions in detail. During the parent information conversation the investigator should clarify whether the infant will fit to the inclusion and exclusion criteria (as described in the “parent information”) to prevent unnecessary non-eligible subjects signing the informed consent. The Principal Investigator must clarify if parents / caregiver are able to understand and speak serbian language fluently to make sure they will understand all aspects relevant for them.

Subjects are recruited, if their parents / caregivers gave written informed consent and if they had been successfully screened for inclusion and exclusion criteria (chapter 5). The phase of recruitment covers the period of day 4 or 5 of life. Subjects recruited for the study will be assigned to a four-digit Subject ID Number starting with a zero (e.g. 0001 – 0300). Assignment to the Subject ID Number is documented on the “Subject Screening List” (Appendix 15.9). The Subjects ID number needs to be transferred to the “Subject Identification List” (Appendix 15.10) as well as the “Subject Randomisation List” (Appendix 15.11). Contact data will be documented on the Subject Identification List. The latter will remain at the study site and may not be forwarded to the sponsor (data protection).

The Subject ID Number will accompany parents / caregivers and subject throughout the study duration. All blood samples as well as all diaries and Visit documentation sheets will be coded with this Subject ID Number.

Subject finally assigned for the formula groups will receive a Formula Random Number as well (chapter 9.6). This number will not replace the Subject ID Number. The Formula Random numbers are 3 digit numbers which will be assigned in ascending order, for girls starting with 101 continuing to 199 and going on with 301. For boys starting with 201 to 299 and proceeding with 401. All subjects finally enrolled (including breastfed infants without Formula Random number) will be documented without contact details in the “Subject Randomisation List”.

Randomisation will be done at best at the Baseline Visit, but can be done until day 14 if parents/caregivers decide -due to any reason not related to this study- to skip breastfeeding during this time. All mothers will be provided with the information that if they against all recommendations decide to stop breastfeeding their infant can be randomised into one of the study formula groups until day 14 of life. Later on they might also be randomised based upon decision of the Principal investigator when the Principal investigator makes sure that mother will be able to fulfil a complete change to study formula not later than day 28.

The Principal Investigator and his study team will do all efforts to enrol a total of 300 subjects within one year – but within 1 ½ year the latest.

## 8.5 Visit

### 8.5.1 Baseline Visit (4-5 days of life)

The Subjects ID Number and date of Visit must be reported on the CRF (Baseline Visit).

#### 8.5.1.1 Inclusion and exclusion criteria

After written consent was given from the parents, inclusion and exclusion criteria (see 5.2 and 5.3) will be assessed and documented in the CRF (Appendix 15.12).

#### 8.5.1.2 Core data

Following core data parameters will be assessed at Baseline:

##### Core Data

- Infant Core data

- Sex
- Date of birth
- Gestation in completed weeks
- Mode of delivery
- Birth weight
- Body length at birth
- Head circumference at birth
- APGAR score
- Care of child (mother, daily nursery,...)

- Core data parents

##### *Mother (only)*

- Date of birth
- First child
- Smoking
- Maternal education (Basic – additional – tertiary)

##### *Mother and father*

- Weight before pregnancy
- Weight at the end of pregnancy (before birth; mother only)
- Weight and height at Recruitment
- Diagnosed Allergies
- Ethnicity (Country of birth, cultural heritage)
- Socioeconomic status (measured by occupation)

Feeding history from birth until recruitment

Following aspects concerning the feeding from birth until recruitment must be documented:

- Type of feeding at recruitment: formula-feeding, breastfeeding
- Duration of exclusively breastfeeding
- Duration of partial breastfeeding
- Duration of exclusively formula-feeding
- Type of formula used so far (brandname)

#### **8.5.1.3 Anthropometric data**

Anthropometric measurement must be performed within the paediatrician's examination as described below (SOP for anthropometric measurements). Always the same paediatrician or member of the study team has to perform this measurement. To assure that variances through different methods of determination are minimized, study team members in the clinic will be trained together at the beginning of the study.

- Body weight (g): measurement will be done with a calibrated scale (seca 336) with a precision of 10 g. The infant, without diaper, is placed on the scales so that the weight is equally distributed on each side of the center of the pan. Weight is recorded, to the nearest 10 g, with the infant lying quietly, which may require patience. The measurement is repeated and recorded twice after excluding any clearly erroneous results.
- Body length: distance crown - sole (cm): Two observers are required to measure recumbent length. The subject lies in a supine position upon seca 232 length. The crown of the head touches the stationary, vertical head-board, and the center line of the body coincides with the center line of the measuring table. The infant's head is held with the Frankfurt Plane aligned perpendicular to the plane of the measuring table. The shoulders and buttocks are flat against the tabletop, with the shoulders and hips aligned at right angles to the long axis of the body. The legs are extended at the hips and knees and lie flat against the tabletop, with the arms resting against the sides of the trunk. The measurer positioning the head stands behind the end of the table to ensure that the subject does not change position and to check the alignment of the body with the long axis of the table. The second measurer makes sure both head and feet touch the headboard while the legs are straightened without forcing them. He places one hand on the knees to ensure that the legs remain flat on the table. He or she applies firm pressure with the other hand to shift the movable board against the heels. The measurement is repeated and recorded twice after excluding any clearly erroneous value. The length is recorded to the nearest 0.1 cm

- Head circumference (cm): An infant is measured when recumbent or seated. For this measurement is used an Insertion tape. The measurer stands facing the left side of the infant and places the tape so that the zero end is on the lateral aspect of the head. This involves passing the tape around the head and then transferring the ends of the tape from one hand to the other so that the zero mark on the tape is inferior to the value to be recorded. The tape is positioned so that large amounts of cranial hair (braids) are excluded. Anteriorly, the tape is placed just superior to the eyebrows and posteriorly it is placed so that the maximum circumference is measured. The plane of the tape must be the same on both sides of the head. The tape is pulled tightly to compress hair and obtain a measure that "approximates" cranial circumference. The measurement is recorded to the nearest 0.1 cm. The measurement is repeated and recorded twice after excluding any clearly erroneous value.

